- h Pregnancy test for women of childbearing potential only. For male subjects with female partners of childbearing potential, pregnancy tests are strongly recommended. Male subjects whose partners are pregnant must be instructed to use a condom to minimize exposure of RBV to the partner. Female subjects of childbearing potential and their male partners must use 2 effective contraceptive methods during treatment and for 4 months after all treatment has ended. Male subjects and their female partners of childbearing potential must use 2 effective contraceptive methods during treatment and for 7 months after all treatment has ended.
- i Serum ( $\beta$ -HCG) pregnancy test at screening and serum or urine pregnancy test before first dose of treatment to ensure that women are not pregnant at the time of starting treatment.
- j For female subjects of childbearing potential, pregnancy testing (serum or urine) should occur monthly during telaprevir combination therapy and for 4 months after all treatment has ended. For male subjects with female partners of childbearing potential, pregnancy testing should occur monthly during telaprevir combination therapy and for 7 months after RBV therapy has ended.
- k If not performed in the past or subject to change at screening.
- l At screening a complete physical examination should be performed. At all other visits up to 30 days after the last dose of telaprevir, physical examinations should be directed at detecting adverse events. All physical examinations performed more than 30 days after the last dose of telaprevir should be completed according to clinical practice.
- m Electrolyte disturbances (eg, hypokalemia, hypomagnesemia, and hypocalcemia) should be monitored and corrected, if necessary, before initiation and during telaprevir therapy.
- n A posttreatment HCV RNA level that is measured at a time point at least 12 weeks after the last dose of treatment may be reported if HCV RNA is not measured at 24 weeks after the last dose of treatment.
- o Drug accountability only for telaprevir.
- p Collect all concomitant therapies for rash and anemia, regardless of adverse event severity grade, and all concomitant therapies for serious adverse events through 30 days after last dose of telaprevir.

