- q Serious adverse events, as described in the protocol, will be recorded in the CRF starting from the first use of telaprevir until 30 days after administration of the last dose of telaprevir.
- r Adverse events reported by subjects after signing of the informed consent and before the first dose of telaprevir and those reported more than 30 days after administration of the last dose of telaprevir should be monitored according to clinical practice and noted in the source document.
- s Only protocol-defined adverse events (see Safety Evaluations in Synopsis), whether serious or non-serious, that occur between the first use of investigational product (telaprevir) and 30 days after administration of the last dose of telaprevir will be reported in the CRF. The DAIDS criteria will be used to grade adverse events except for rash which has protocol-specific definitions of severity grades.
- t Special reporting situations (eg, overdose, suspected abuse/misuse, inadvertent or accidental exposure, or medication error of telaprevir) and Product Quality Complaints (PQCs) should be reported in addition to adverse events.

$\beta$ -HCG= $\beta$ -human chorionic gonadotropin; CRF=case report form; DAIDS=Division of AIDS Table for Grading the Severity of Adult and Pediatric Adverse Events; HbsAg=hepatitis B surface antigen; HCV=hepatitis C virus; HIV=human immunodeficiency virus; Peg-IFN-alfa=pegylated interferon alfa; RBV=ribavirin; RNA=ribonucleic acid.

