### **Adverse Events**

The verbatim terms used in the CRF by investigators to identify adverse events will be coded using the Medical Dictionary for Regulatory Activities (MedDRA). All reported adverse events with onset during the treatment phase (ie, treatment-emergent adverse events, and adverse events that have worsened since baseline) will be included in the analysis. For each adverse event, the percentage of subjects who experience at least 1 occurrence of the given event will be summarized by treatment group.

Only adverse events as defined in Section 12.3.1, All Adverse Events, whether serious or non-serious, that occur between the first use of investigational product (telaprevir) and 30 days after administration of the last dose of telaprevir will be collected and summarized. Particular attention will be given to adverse events of special interest, eg, rash and anemia.

Summaries, listings, datasets, or subject narratives may be provided, as appropriate, for those subjects who die, who discontinue treatment due to an adverse event, or who experience a severe or a serious adverse event.

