### **12.3. Procedures**

#### **12.3.1. All Adverse Events**

All adverse events, as defined below, which occur between the first use of investigational product (telaprevir) and 30 days after administration of the last dose of telaprevir will be recorded in the CRF. Serious adverse events, including those spontaneously reported to the investigator more than 30 days after the last dose of investigational product (telaprevir), must be reported using the Serious Adverse Event Form. The sponsor will

evaluate any safety information that is spontaneously reported by an investigator beyond the time frame specified in the protocol.

The DAIDS criteria will be used to grade all adverse events except for rash which has protocol-specific definitions of severity grades provided in Section 9.3.1.1.1.

The following adverse events will be recorded in the CRF:

- Adverse events of special interest
  - All rash and anemia events, regardless of DAIDS grade or relationship to telaprevir
- The following which are considered at least possibly related to telaprevir by the investigator
  - All adverse events, including laboratory abnormalities, with DAIDS grade 2 (moderate) or higher
  - Other adverse events (ie, DAIDS grade 1 [mild]), including laboratory abnormalities, considered medically significant (eg, require medical intervention)
- All adverse events leading to discontinuation of telaprevir, regardless of DAIDS grade or relationship to telaprevir
- All serious adverse events, regardless of relationship to telaprevir
- Any pregnancy in female subjects or in female partners of male subjects; see Section 12.3.3
- Special reporting situations: overdose, suspected abuse/misuse, inadvertent or accidental exposure, or medication error of telaprevir; see Section 12.2
- Other adverse events will be recorded as per local regulations only

All adverse events, as defined above, must be recorded using medical terminology in the source document and the CRF. Whenever possible, diagnoses should be given when signs and symptoms are due to a common etiology (eg, cough, runny nose, sneezing, sore throat, and head congestion should be reported as “upper respiratory infection”). Investigators must record in the CRF their opinion concerning the relationship of the adverse event to study therapy. All measures required for adverse event management must be recorded in the source document and reported according to sponsor instructions.

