### **12.3.2. Serious Adverse Events**

All serious adverse events occurring during clinical studies must be reported to the appropriate sponsor contact person by investigational staff within 24 hours of their knowledge of the event.

Information regarding serious adverse events will be transmitted to the sponsor using the Serious Adverse Event Form, which must be completed and signed by a member of the investigational staff, and transmitted to the sponsor within 24 hours. The initial and follow-up reports of a serious adverse event should be made by facsimile (fax).

All serious adverse events that have not resolved by the end of the early access program, or that have not resolved upon discontinuation of the subject's participation in the early access program, must be followed until any of the following occurs:

- The event resolves
- The event stabilizes
- The event returns to baseline, if a baseline value/status is available
- The event can be attributed to agents other than the study drug or to factors unrelated to the conduct of the early access program
- It becomes unlikely that any additional information can be obtained (subject or health care practitioner refusal to provide additional information, lost to follow-up after demonstration of due diligence with follow-up efforts)

Suspected transmission of an infectious agent by a medicinal product will be reported as a serious adverse event. Any event requiring hospitalization (or prolongation of hospitalization) that occurs during the course of a subject's participation in this early access program must be reported as a serious adverse event, except hospitalizations for the following:

- Conditions which existed prior to the trial and which did not deteriorate during the trial
- Treatment or care of hepatitis C diseases unless fatal or considered to be related to telaprevir
- Investigational or elective procedures

Hepatitis C infection is characterized by a series of infections and neoplasms, which depending on the disease stage of the subject may constitute a life-threatening event. Reporting all such events as serious adverse events could divert attention from the serious adverse events that could be related to the study drug. Therefore for this early access

program the following occurrences will NOT be recorded or reported as serious adverse events:

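### Footnote r of the Time and Events Schedule sorts late adverse events by report date, while the rest of the protocol defines the CRF window by occurrence; in-window events first told at Week 24 get contradictory instructions

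*Protocol*

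**What the plan says.** **Occurrence rule.** Section 12.3.1 sends to the CRF "All adverse events, as defined below, which occur between the first use of investigational product (telaprevir) and 30 days after administration of the last dose". Footnote s, on the adverse event row of the Time and Events Schedule, limits CRF reporting to protocol-defined events "that occur between the first use of investigational product (telaprevir) and 30 days after administration of the last dose of telaprevir". The Synopsis (Safety Evaluations), Section 9.3 and the second paragraph on adverse events in Section 11.5 use the same window.

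**Report-date rule.** Footnote r says that "those reported more than 30 days after administration of the last dose of telaprevir should be monitored according to clinical practice", with a source-document note. It marks the Week 24, Week 48, early discontinuation/withdrawal and follow-up cells of both the adverse event and the serious adverse event rows, as well as the screening and baseline cells.

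**Visits.** After Week 12 the next scheduled visit is Week 24, which footnote c makes a recommended time point. Section 9.3.1.1.3 dates the end of the 30 days at Week 16 or earlier.

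**Therapies.** Footnote p asks for rash and anemia therapies and "all concomitant therapies for serious adverse events through 30 days after last dose of telaprevir". That row has no tick at Week 24 or Week 48.

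**Serious events.** Section 12.3.1 says that serious adverse events, including those spontaneously reported after the 30 days, "must be reported using the Serious Adverse Event Form". Section 12.3.2 requires all serious adverse events to reach the sponsor within 24 hours and gives no end date. It adds that, with listed exceptions, any event requiring hospitalization "that occurs during the course of a subject's participation in this early access program must be reported as a serious adverse event".

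**Analysis.** The first paragraph on adverse events in Section 11.5 includes "All reported adverse events with onset during the treatment phase". The second restricts collection and summary to the 30-day window.

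**The concern.** Collecting safety and tolerability data is the program's only data objective, so the recording window should have one definition. Occurrence and report date give the same answer only when an event is told before the window closes. For a subject who finishes telaprevir, the schedule offers no routine visit between the last dose and that closing date. The first scheduled question about the 30-day tail therefore comes at a visit whose cell carries footnote r. A site that follows footnote s enters a Week 14 event in the CRF; a site that follows footnote r may leave it in the source notes. If sites differ, the recorded incidence of rash, anemia and serious adverse events in the tail depends partly on which footnote each site reads. A larger sample does not reduce that kind of error.

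**Working it through.** **1. The plan's own figures.** With Week n taken as day 7n, the planned last telaprevir dose falls on day 84. Then 84 + 30 = 114 and 114/7 = 16.3, which agrees with the Week 16 in Section 9.3.1.1.3. For the precision table in Section 11.4 at a 10% event rate and 3,000 subjects, 1.96 × √(0.10 × 0.90 / 3,000) = 1.07 points (stated: 1.1).

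**2. The stretch without a scheduled visit.** This assumes a subject who stays on Peg-IFN-alfa/RBV and attends the scheduled visits.

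| Last telaprevir dose (day) | Window closes (day) | Last scheduled visit inside | Window days after it | Next visit |
|---|---|---|---|---|
| 84 (completer) | 114 | Week 12 | 30 | Week 24 |
| 77 | 107 | Week 12 | 23 | Week 24 |
| 70 | 100 | Week 12 | 16 | Week 24 |
| 56 | 86 | Week 12 | 2 | Week 24 |
| 53 | 83 | Week 8 | 27 | Week 12 |
| 28 | 58 | Week 8 | 2 | Week 12 |

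For a completer the tail is 30/114 = 26% of the window. Week 24 is day 168, which is 168 − 84 = 84 days after the last dose and 168 − 114 = 54 days after the window closes. In the last two rows the next visit is Week 12, whose cells do not carry footnote r. A subject who stops all three drugs has a discontinuation visit and a follow-up visit 24 weeks after the last dose. How much of the tail is then unvisited depends on when the discontinuation visit is held, which the protocol does not fix.

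**3. One event under both rules.** Take a protocol-defined event with onset at Week 14 (day 98) in a completer, first mentioned at Week 24.
- By occurrence (footnote s, Section 12.3.1): 98 − 84 = 14 days after the last dose, so inside the window and entered in the CRF.
- By report date (footnote r): told 84 days after the last dose, so left to clinical practice and the source document.

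**4. Possible size.** The protocol gives no timing of events, so this is an illustration. Take a true serious adverse event rate of 10%, the example in Section 11.4. Let s be the share of affected subjects whose event falls only in the tail, and u the fraction of those left out of the CRF. The observed rate is 10 × (1 − s × u).

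| s | u | Observed (%) | Bias (points) |
|---|---|---|---|
| 5% | 25% | 9.88 | 0.12 |
| 10% | 50% | 9.50 | 0.50 |
| 26% (constant rate over 114 days) | 25% | 9.34 | 0.66 |
| 26% | 50% | 8.68 | 1.32 |
| 26% | 100% | 7.37 | 2.63 |

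The bias passes the half-width once s × u exceeds 1.07/10, that is, when about 11% of all affected subjects go unrecorded.

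**5. Late serious events.** Footnote r on that row names clinical practice and the source document. Section 12.3.1 names the Serious Adverse Event Form for spontaneously reported late events, and Section 12.3.2 sets a 24-hour duty without an end date. Footnote r does not forbid the form, but it gives a site working from the schedule no pointer to it.

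**The case against.** The best defence is that five places use occurrence and only one footnote uses report date. Footnote s, on the same row, still sends a late-told in-window event to the CRF, and no passage says such an event is to be left out. Section 9.3 has subjects asked about events at every visit, so Week 24 is covered. Section 9.3.1.1 tells subjects to contact the site immediately about a skin reaction, extra visits are allowed, and Section 8 requires rash and anemia therapies through the 30 days to be recorded whatever the schedule ticks. All of this stands. A reader might infer that events in the tail are lost; the documents support only conflicting instructions and possible under-recording.

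A reader might also see a third window in Section 11.5 that drops events starting after all drugs are stopped. The next paragraph there already states the 30-day window, so at most two adjacent paragraphs need aligning. They differ in practice only for subjects who stop all drugs early, because in the others Peg-IFN-alfa/RBV continues for 12 or 36 weeks and the tail lies inside the treatment phase.

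On serious events, the CRF and the Serious Adverse Event Form are separate instruments, and Section 12.3.1 limits its late-event clause to spontaneous reports. The mismatch is therefore one of unclear wording, and it is not shown that sites would leave such events unreported.

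The defence does not remove the report-date wording from the very cells a site reads at Week 24.

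**Conclusion.** The concern holds as an internal contradiction in data-capture rules. Footnote r sorts by report date, the rest of the protocol by occurrence, and for telaprevir completers the schedule makes the difference matter. The stretch at issue is at most 30 of 114 days; it is shorter for most subjects who stop telaprevir early.

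The bias cannot be fixed from the protocol. The 0.1 to 2.6 points rest on an assumed 10% rate, 5% to 26% of affected subjects having their event only in the tail, and 25% to 100% of those going unrecorded. A reader might infer a loss of 1.4 to 2.5 points: with zero capture in the tail, 1 − 0.9^(84/114) = 7.5% under a constant hazard, or 1 − 0.9^(84/99) = 8.6% if the hazard halves after telaprevir. Those are bounds for completers under hazards the protocol does not give, and they ignore every other capture route listed above. They should not be read as an expected under-count.

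The program is descriptive and tests no hypothesis, so no inference is overturned. The reason to act is that safety incidence is what the program will report.

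**What to change.** - In footnote r, replace *reported* by *with onset* for the limit after telaprevir. The pre-dose limit can stay, since Section 12.1.1 starts collection at first use.
- Add to footnote r that serious adverse events occurring after the first telaprevir dose follow Sections 12.3.1 and 12.3.2, including their hepatitis C exclusions, whenever they are reported. A blanket instruction to put every serious event on the form would be too broad, because it would override those exclusions and reach pre-dose events.
- At the existing Week 24 visit, record in the CRF protocol-defined events with onset up to 30 days after the last telaprevir dose, and the rash, anemia and serious adverse event therapies given in that window. Mark the Week 24 cells accordingly. A telephone contact near day 30 would be an optional addition.
- In Section 11.5, align the first paragraph on adverse events with the second: first telaprevir use to 30 days after the last dose.

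The cost is footnote and paragraph wording plus one question at a visit already in the schedule. Treatment and clinical management are unaffected.

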## ABBREVIATIONS

|                   |                                                                                       |
|-------------------|---------------------------------------------------------------------------------------|
| AGEP              | acute generalized exanthematous pustulosis                                            |
| ALT               | alanine aminotransferase                                                              |
| AST               | aspartate aminotransferase                                                            |
| β-hCG             | β-human chorionic gonadotropin                                                        |
| CRF               | case report form                                                                      |
| CI                | confidence interval                                                                   |
| CYP               | cytochrome P450                                                                       |
| DAA               | direct acting antiviral                                                               |
| DAIDS             | Division of AIDS Table for Grading the Severity of Adult and Pediatric Adverse Events |
| DRESS             | drug-related eosinophilia with systemic symptoms                                      |
| DS                | delayed start                                                                         |
| eDC               | electronic data capture                                                               |
| ECG               | electrocardiogram                                                                     |
| EM                | erythema multiforme                                                                   |
| GCP               | Good Clinical Practice                                                                |
| GGT               | gamma-glutamyltransferase                                                             |
| HCC               | hepatocellular carcinoma                                                              |
| HCV               | hepatitis C virus                                                                     |
| HIV               | human immunodeficiency virus                                                          |
| ICH               | International Conference on Harmonisation                                             |
| IEC               | Independent Ethics Committee                                                          |
| IRB               | Institutional Review Board                                                            |
| Peg-IFN           | pegylated interferon                                                                  |
| PQC               | Product Quality Complaint                                                             |
| q8h               | every 8 hours                                                                         |
| RBV               | ribavirin                                                                             |
| RNA               | ribonucleic acid                                                                      |
| SJS               | Stevens-Johnson syndrome                                                              |
| SVR               | sustained virologic response                                                          |
| SVR 24 | sustained virologic response 24 weeks after last dose of study drug                   |
| TEN               | toxic epidermal necrolysis                                                            |
| WBC               | white blood cell                                                                      |
| WT                | wild type                                                                             |

## DEFINITION OF TERMS

|                                  |                                                                                                                                                                                                                                                                                                                                                                                                                            |
|----------------------------------|----------------------------------------------------------------------------------------------------------------------------------------------------------------------------------------------------------------------------------------------------------------------------------------------------------------------------------------------------------------------------------------------------------------------------|
| End of treatment with study drug | Week 12 (telaprevir)                                                                                                                                                                                                                                                                                                                                                                                                       |
| End of treatment with all drug   | Treatment naïve or prior treatment relapsers with severe fibrosis (Metavir F3 or Ishak 3-4): Week 24 or 48, depending on virologic response or early discontinuation.
Previously treated subjects with prior partial or prior null response, or who had viral breakthrough, with severe fibrosis (Metavir F3 or Ishak 3-4) and all subjects with cirrhosis (Metavir F4 or Ishak 5-6): Week 48 or early discontinuation. |
| Standard-of-care treatment       | Treatment with Peg-IFN-alfa and RBV for 24 or 48 weeks                                                                                                                                                                                                                                                                                                                                                                     |
| Stopping rules                   | 
 
• Telaprevir should be discontinued if HCV RNA is >100 IU/mL at Week 4.
 
• Peg-IFN-alfa/RBV should be discontinued if HCV RNA is >100 IU/mL at Week 12.
 
• Beyond Week 12, refer to the local prescribing information for Peg-IFN-alfa and RBV.
 
                                                                                                    |

